## **2 RATIONALE**

The longstanding issues with low coverage in NE and NCL London provide an impetus to start offering self-sampling ahead of the national screening programme. In England, there is a national cervical screening programme offered to all women aged 25-64 using a call/recall system (i.e. women are invited on a regular basis at set intervals). A challenge with introducing new tests into call/recall-based screening programmes is establishing robust pathways for accurately identifying the relevant population, recording and reporting test results and setting the correct recall intervals. It is important to understand how new interventions might work in “real world” settings and to test approaches to improve them before moving to a larger scale. This will be an implementation feasibility trial of offering HPV self-sampling in North East and Central London and is a collaboration between King’s College London, the North Central and East London Cancer Alliance and NHS England London.

The project will serve to test the new pathways for delivery, establish robust pathways for accurately identifying the relevant population, recording and reporting test results and setting the correct recall intervals, generate lessons to help ensure a smooth transition for a national or London-wide roll-out and provide the evidence-base for implementing self-sampling at scale. This will include all the necessary changes to call/recall within NHAIS, NHS laboratories and GP records. Self-sampling kits will be offered to non-attenders via direct mail-out (identified via NHAIS) and opportunistically in GP primary care when they consult for any reason (by GPs, practice nurses or healthcare practitioners/assistants).

Little is known about the specific barriers that this approach to screening overcomes, or about the characteristics of the non-attenders who take up the offer of completing a self-sample test. Previous research by Waller *et al.* has shown that cervical screening non-attenders are a heterogeneous group, including women who have never heard of screening, those who have never engaged with the idea of taking part, those who are undecided, those who have made a conscious decision not to attend, and those who are positively inclined towards screening but are currently overdue.(3)

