| To ensure robust pathways are established for accurately identifying non-attenders for mail-out and opportunistic offer                              | Proportion of women accurately identified for (i) mail-out and (ii) opportunistic offer                                                                                        | Number of women who are correctly (i.e. eligible) and incorrectly (i.e. ineligible) identified in NHAIS as eligible for 15m mailout (NHAIS data) and (ii) ≥6m overdue cervical screening in GP primary care (GP and NHAIS data) as a % of all women identified for (i) 15m mailout and (ii) opportunistic offer, respectively (GP and NHAIS data)                                                                 |
| To assess the demographic characteristics, cervical screening status and previous barriers to screening uptake of women who respond to self-sampling | Uptake of cervical screening by age bands, ethnic group, LSOA, cervical screening status (never screened, overdue, up-to-date) and reported reason for previous non-attendance | Number of women who return a self-sample in (i) 10 year age bands (NHAIS data), (ii) British Census ethnicity categories (GP record and survey data), (iii) cervical screening status (NHAIS data) and (iv) reason for previous non-attendance (survey data) as a % of all women who return a self-sample                                                                                                         |
| To estimate the impact of offering self-sampling on long-term coverage (Long-term follow-up: future analysis)                                        | Coverage at 13 months after trial recruitment ends                                                                                                                             | 
“Coverage” calculated at 13 months after last woman was sent/given a kit (NHAIS data) calculated separately for 3 different groups of women:
 
 
1) 0-14m (women overdue but who were not sent a kit),
 
2) 15m+ (women overdue who were sent a kit),
 
3) 16-26m (women overdue but not sent a kit because past 15m timepoint at trial start)
 
 |

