### **7.2 Participant identification**

#### **7.2.1 Direct mail-out**

Under a Section 251 exemption, eligible women will be identified using the national cervical screening database NHAIS (National Health Application and Infrastructure Services - owned by NHS England and PHE who are the data controllers for the cervical screening database). Accessing these data is the most accurate way of identifying eligible women and ensuring that the women invited to the trial are the appropriate population (i.e. women from a participating GP practice).

Once each GP practice has received training as detailed in section 7.1.2; the study team will issue confirmation for the GP practice to be included in the monthly mailout.

At the start of each month, the study team will then provide NHAIS with a table of participating GP practices. Following receipt of this table; a list of women (from participating GP practices) who reach the 15-month anniversary of their last test due date without being screened (by self-sample or

conventional cervical screening (HPV primary testing or cytology) will be extracted from NHAIS. This 15-month timepoint has been chosen as an approximate midpoint between the usual call/recall screening invitation and reminder letters. This is to make it obvious to women that the self-sampling offer is different from the usual screening invitation and also to avoid overwhelming women with letters about screening. Other than this, the 15-month timepoint is arbitrary, and could equally be taken at a similar timepoint (e.g. 18 months).

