#### **10.4.4 GP record datasets**

Electronic GP record data will provide key data for the trial that are not available from the other data sources, such as ethnicity, granular details of the opportunistic offer (kits offered, accepted and declined, reasons for declining kits, and health professional type offering kits).

Cervical screening (dates and results) data will be obtained to enable us to assess how accurate GP records are for identifying women eligible for the opportunistic offer (it may be that kits may be offered to women who are  $\geq 6$ m according to their GP records but not in NHAIS. Also, cervical screening data in GP records may contain details of tests taken in other countries which are not recorded in NHAIS.

EMIS searches will be written to exclude women who are coded to have opted out from data usage for the study (see section 7.3.5).

GP record data will be extracted in bulk using EMIS searches that have been specially written for the trial. Extracts are likely to be downloaded from participating GP practices once they sign up to the trial (historical cohort data), at the end of the trial and depending on logistics, at several points during the study (e.g. on a monthly basis, at the end of active recruitment). These data extracts will be downloaded centrally at the CCG level by a member of the relevant CCG. If central download is

not possible, it will be carried out by each GP practice by a member of the practice team. The Clinical Effectiveness Group (CEG) have confirmed that they have centralised access to all GP practice data in Tower Hamlets and Newham CCG. Similarly, North East London Commissioning Support Unit (NEL CSU) have access to data from all GP practices in Barnet and Islington CCGs. Camden CCG have an IT lead who we plan to liaise with to extract data for Camden GP practices.

De-personalised line-level data will be collected for all women who are eligible (i.e.  $\geq 6m$  overdue cervical screening) and therefore, will include data from women who have not consented to the trial.

CAG approval will be sought to allow download of identifiable data at the CCG level and to allow the trial team at KCL to access de-personalised line-level data from women who have not consented to the trial. The CCG IT team will encrypt the NHS numbers before securely sending the data to King's.

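### The measure of how accurately non-attenders are identified counts only women already identified, so it cannot show those missed; its mail-out limb also cannot show ineligibility that NHAIS does not record

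*Protocol*

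**What the plan says.** Protocol Section 2 gives as a purpose of the project to "establish robust pathways for accurately identifying the relevant population". Section 3.2 turns this into an exploratory objective: "To ensure robust pathways are established for accurately identifying non-attenders for mail-out and opportunistic offer". The endpoint is "Proportion of women accurately identified for (i) mail-out and (ii) opportunistic offer".

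The measure has two limbs.

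- **Mail-out.** It counts women "correctly (i.e. eligible) and incorrectly (i.e. ineligible) identified in NHAIS as eligible for 15m mailout (NHAIS data". The list being checked is itself an NHAIS extract of women "who reach the 15-month anniversary of their last test due date without being screened" (Section 7.2.1).
- **Opportunistic offer.** It counts women identified as "≥6m overdue cervical screening in GP primary care (GP and NHAIS data", so two sources are named.

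Both are then expressed "as a % of all women identified for (i) 15m mailout and (ii) opportunistic offer, respectively (GP and NHAIS data".

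On the data sources, Section 10.4.1 regards NHAIS as the better source of screening data. Section 10.4.4 adds that "cervical screening data in GP records may contain details of tests taken in other countries which are not recorded in NHAIS".

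**The concern.** A pathway that is meant to find non-attenders can fail in two ways. It can pick women who should not be picked, or it can overlook women who should be. A percentage of women identified responds only to the first kind of failure. If the trial reports this figure as identification accuracy, an alert or list that overlooks many eligible women could still look sound, and that reading would feed the lessons for wider roll-out described in Section 2.

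The mail-out limb has a second weakness. The named reference is the database that produced the list, so an error or gap in the NHAIS record appears identically on both sides of the comparison and cannot be seen.

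**Working it through.** **No figure to reproduce.** The protocol gives no target or expected value for this measure. Only the scale can be checked. Section 9.1.1 assumes 106 practices, 20 women per practice per month and 9 months on average: 106 × 20 × 9 = 19,080, against the stated approximately 19,000.

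**Missed women.** Let N be the women identified, E the eligible women among them, and m the share of all eligible women who are missed.

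- Measure as written = E / N. It contains no m.
- All eligible women = E / (1 − m). Sensitivity = 1 − m.

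Take N = 19,080 and assume 95% are eligible, so E = 0.95 × 19,080 = 18,126. Both the 95% and the values of m are assumptions.

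| m | All eligible, 18,126 / (1 − m) | Missed | Measure as written | Sensitivity |
|---|---|---|---|---|
| 0% | 18,126 | 0 | 95.0% | 100% |
| 10% | 20,140 | 2,014 | 95.0% | 90% |
| 30% | 25,894 | 7,768 | 95.0% | 70% |
| 50% | 36,252 | 18,126 | 95.0% | 50% |

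The algebra is the same for the opportunistic limb.

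**Wrongly mailed women.** Let w be the share of mailed women who are truly ineligible, and d the share of those whose ineligibility shows in NHAIS data. The measure as written is 1 − w × d, and the true predictive value is 1 − w. Again w and d are assumed.

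| w | d = 0 | d = 0.25 | d = 0.5 | d = 1 (true value) |
|---|---|---|---|---|
| 5% | 100% | 98.75% | 97.5% | 95% |
| 10% | 100% | 97.5% | 95% | 90% |
| 20% | 100% | 95% | 90% | 80% |

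**What NHAIS can and cannot show.** The line-level fields in Section 10.4.1 include age, test dates and results, mail-out identification date, disclaimer status and practice. They can reveal a mailed woman who was the wrong age, already screened, had a disclaimer on file or belonged to a non-participating practice, so d is above zero for such errors. Two kinds of ineligibility may stay hidden:

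- tests abroad held only in GP records (Section 10.4.4);
- recent colposcopy care or a test of cure being due. This is an exclusion in Section 6.2, but Section 10.4.1 lists no field for colposcopy care. The colposcopy extract in Section 10.4.3 covers only women who return a sample, and only later events.

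The laboratory's count of ineligible women (Section 10.4.2) is confined to returned samples. At the 15% mail-out return assumed in Section 9.1.1, 1 − 0.15 = 85% of mailed women would never reach that check.

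**Can misses occur?** The alert in Section 7.2.2 requires a gap of 3.5 or 5.5 years without a recorded test and no hysterectomy or cervical amputation code. A woman with a wrong code would be overdue but unflagged. So could a woman on annual recall, whom Section 6.2.3 places in the opportunistic route only: on her own interval she is six months overdue at 12 + 6 = 18 months, well before the alert's threshold. The documents say nothing about how many such women there are.

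**The case against.** The strongest reply has five parts.

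1. *The measure does count ineligible women.* This stands. A reader might infer that, because list and check share a database, the mail-out figure must sit near 100% however many women are wrongly mailed. The documents do not support that. It requires d = 0, whereas the listed NHAIS fields can expose extraction errors, and Section 12.1.2 names the NHAIS programming changes as a main delivery risk.
2. *Out-of-date GP records lead to over-flagging.* This also stands. A reader might infer that stale records make missed women likely. But the alert fires when no recent test is recorded, so a missing result mainly produces a wrong flag, which a predictive value does detect. Section 10.4.4 expects that direction.
3. *NHAIS is the better source, so GP records should not judge it.* This stands as a limit on the remedy: disagreement can be reported, but GP records should not be the gold standard.
4. *Part of the check is already planned.* True. Comparing flagged women with NHAIS is what the opportunistic limb specifies. The closing mention of GP and NHAIS data could also be read as allowing GP data for the mail-out, although the limb itself names NHAIS alone.
5. *The endpoint is exploratory and has no decision rule.* True, and it limits the consequence.

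None of this restores the missed women to the denominator.

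**Conclusion.** The concern holds in a limited form. On both routes the measure is a positive predictive value and does not change with the share of eligible women missed. This follows from the stated denominator and needs no assumption. On the mail-out route, as written, it can show extraction errors but not ineligibility absent from NHAIS, and the closing source wording leaves it unclear whether GP data may be used.

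The size cannot be stated. A reader might want to put a number on women missed among the roughly 95,000 eligible (Section 9.1), but the documents give no miss rate. The values of m, w and d, and the 95%, are illustrative only. The primary endpoints are unaffected. The change is still worth making, because this row of Section 3.2 is where the trial measures whether its pathways find the relevant women.

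**What to change.** In Section 3.2, keep the predictive value, call it that, and say which source judges each limb. Add three quantities:

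- **(a) Missed by the GP route.** Women at least six months overdue in the NHAIS line-level extract who are absent from the GP-record eligible list at a matching date, as a percentage of all NHAIS-overdue women at participating practices. Some may be correctly absent because the GP holds a test from abroad, so describe this as possible misses.
- **(b) Missed by the mail-out.** Women whose NHAIS record shows they reached 15 months unscreened at a practice then in the mail-out, but who have no mail-out identification date or no kit-sent record, as a percentage of all such women. Set aside women with a disclaimer on file, whom Section 6.2.2 excludes. This finds failures between record and mailing, not errors in NHAIS itself.
- **(c) Source disagreement.** The proportion of mailed women whose linked GP record disagrees with NHAIS on eligibility, reported as disagreement and not as GP records correcting NHAIS.

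The cost is a wording change and somewhat more linkage and cross-tabulation. The NHAIS, GP and mailing extracts are already planned and carry the study ID (Sections 10.4.1, 10.4.4 and 10.4.5). One point needs checking: the GP extract covers women overdue according to GP records, so a mailed woman with a test known only to her GP may appear as absent from it rather than as a recorded conflict. Item (c) should count such absences separately.

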| To examine in more detail the opportunistic offer of self-sampling in GP primary care (if data allow)                                                                                                                                                                              | 
Response rates of eligible women offered kits in GP primary care
 
Reasons for declining kits
 
Kit offer and response to offer by health care professional type
 | 
The number of women who (i) accept a kit or (ii) decline a kit as a % of total number of eligible women offered kits opportunistically in GP primary care (GP record data)
 
Aggregated data on the main reasons for declining kits (GP records): number of women with each key reason provided as a % of all women recorded as declining kits (GP record data)
 
Number of kits (i) offered and (ii) accepted by health care professional type as a % of all kits offered (GP record data)
 |
| To assess any potential “nudge” effect towards the uptake of conventional screening associated with offering self-sampling                                                                                                                                                         | Uptake of conventional screening within 3 months of offer of self-sampling                                                                                                        | 
At participating GP practices:
 
Number of women who attend for conventional screening (and do not return a self-sample) within 3 months of the date of 15-month mailout pre-notification letter is sent (NHAIS &
                                                                                                                                                                                                                                                                            |

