### 7.2.2 Opportunistic offering

Women targeted for opportunistic offering will be identified using the GP patient record software system (date of last recorded cervical screening test). Although cervical screening records in GP records are sometimes not up to date, this method of identifying the relevant cohort for opportunistic offering is currently the only viable option (GP patient records are not linked to the national screening database (NHAIS)).

An alert will be set up on the electronic patient record (EPR) software to automatically flag potentially eligible women when their record is opened. Specifically, EPR systems will be programmed to flag women aged 25.5-64 years who are at least 6 months overdue cervical screening (i.e. no cervical screening test (cytology, HPV primary or self-sample) recorded in the past 3.5 years (if aged 25-49) or 5.5 years (if aged 50-64) and no codes for hysterectomy or amputation of cervix). The alert will be switched on at the practice start date.

Doctors, nurses and healthcare assistants (HCA)/assistant practitioners (AP) will be asked to offer self-sampling kits to women who have been flagged when they consult for any reason. In practice, this will be on a case-by-case basis at the discretion of the healthcare professional consulted. The trial invitation (kit offer) will comprise a brief conversation (~2 minutes) at the end of the consultation. Healthcare professionals will be asked to confirm the women's eligibility before handing them a self-sampling kit, which includes the patient information booklet.

A study template will be set up in the GP electronic patient record system. When women are offered kits, the consulting health professional will use the template to record:

- 1) Whether or not the trial kit was accepted.

- 2) If accepted: trial kit ID number
- 3) If declined:
  - a) Reason for declining (if logistics allow)
  - b) Consent or dissent to share anonymous data from their GP records and the national cervical screening database

If the woman accepts a kit, the consulting health professional will:

- Print out a lab request/consent form with the woman's details mail-merged using the EPR system to be returned with the sample
- Write the kit ID number on the lab request/consent form
- Write three of the NHS CSP acceptable identifiers on the tube label. Preferably these will comprise the woman's name, date of birth and postcode.

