### 9.1.3 Questionnaire-based sub-study

As the trial is designed to be descriptive, a formal power calculation is not possible. A previous study in Westminster, London(18) had a survey response rate of 97% among the 6% of women who completed a self-sample kit, and just under 1% for those who did not send back a kit. We therefore expect a very low response rate in women who do not return the kit, making statistical comparisons between completers and non-completers inappropriate. However, we plan to explore demographic patterns of PAPM stage, previous barriers and confidence in completing the kit (e.g. by ethnicity and level of deprivation) within the completer and (to a lesser extent) the non-completer groups, and to do this, we anticipate needing a relatively large sample.

We have allowed for a high response rate (90% for kit completers; 10% for non-completers) to avoid under-funding. This would yield a sample of ~5,500 kit completers and ~2,500 non-completers but we anticipate the actual sample size is likely to be somewhat lower.

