**Table 3 Summary of anticipated sub-study sample**

|                                           |        |
|-------------------------------------------|--------|
| Total questionnaires sent:                | 31,000 |
| Total returned from kit completers (90%): | 5,580  |

|                                               |       |
|-----------------------------------------------|-------|
| Total returned from kit non-completers (10%): | 2,480 |
| Total questionnaires returned                 | 8,060 |

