#### **10.4.6 Questionnaire dataset**

Questionnaires will be returned to the King's trial team directly from women via the post. They will be pre-printed with the kit ID number. The kit ID number will be used to link questionnaire answers to the woman's cervical screening history, HPV result and (if HPV positive) attendance for follow-up, as well as basic demographic information not collected as part of the questionnaire e.g. age, LSOA. Kit ID numbers with corresponding study ID numbers (encrypted NHS number) will be provided by HSL and CFH Docmail.

Data collected in the questionnaire include self-reported data on previous screening barriers and future screening preferences.

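### Reasons for previous non-attendance come only from the survey but are divided by all self-sample returners, so each is understated by the share who did not answer (about 3% to 10% in relative terms)

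*Protocol*

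**What the plan says.** **Survey reasons.** The last part of the section 3.2 table has an exploratory row on the demographic characteristics, screening status and previous barriers of women who respond to self-sampling. Its measure covers age band, ethnicity, screening status and "iv) reason for previous non-attendance (survey data) as a % of all women who return a self-sample". Age and screening status come from NHAIS and ethnicity from GP records and the survey. The reason for previous non-attendance has the survey as its only named source.

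Section 10.4.6 confirms that source: "Data collected in the questionnaire include self-reported data on previous screening barriers and future screening preferences". Under section 4.5 women are invited to complete the questionnaire and post it to the trial team, while the swab goes to the laboratory. A woman can therefore return one without the other.

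**Expected response.** Section 9.1.3 says that an earlier study in Westminster "had a survey response rate of 97% among the 6% of women who completed a self-sample kit". For this trial it states: "We have allowed for a high response rate (90% for kit completers; 10% for non-completers) to avoid under-funding". It adds that "we anticipate the actual sample size is likely to be somewhat lower".

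**Decline reasons.** A separate exploratory row on the opportunistic offer, to be done only if the data permit, reports the "number of women with each key reason provided as a % of all women recorded as declining kits", from GP records. Section 7.2.2 lists among the template fields for a woman who declines: "Reason for declining (if logistics allow").

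**The concern.** A woman who sends a swab but no questionnaire can never enter the numerator of a reason, yet she always enters the denominator. In effect she is counted as not having the reason, although she was never heard from. The percentage then mixes how common a barrier is with how many women answered. An all-returner denominator suits the items held in NHAIS; it does not suit the one item that depends on a voluntary form.

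The same table handles another item from this questionnaire differently: preferred future screening method is divided by women who returned a survey. Barriers also feature in the questionnaire sub-study (section 9.2.4), which works from the women who responded. The same barrier could thus appear in the trial's reports with two different percentages.

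The decline reasons have the same structure if the reason field is left blank for some women. At stake is the accuracy of a descriptive profile meant to inform whom to target. No test, decision rule or primary result depends on it.

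**Working it through.** **1. Inputs**
- Completer survey response: 97% (earlier study) and 90% (budget allowance), both section 9.1.3.
- Questionnaires sent 31,000; from completers 5,580; from non-completers 2,480; total 8,060 (Table 3).
- Opportunistic offers about 17,100; acceptances about 12,000 (section 9.1.2).
- Illustrative true prevalence of a reason: 40% (my assumption; the protocol gives none).

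**2. Reproducing the protocol's own figure.** Table 3 gives 5,580 in the row "Total returned from kit completers (90"%). The completer share is not stated but can be solved: 5,580 / 0.90 = 6,200, and 6,200 / 31,000 = 20%. The other row agrees: (31,000 − 6,200) × 0.10 = 2,480, and 5,580 + 2,480 = 8,060. On the protocol's own plan, 6,200 − 5,580 = 620 women return a swab and no questionnaire.

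**3. Size of the understatement.** Let p be the true proportion with a reason and r the fraction of self-sample returners who answered. If those who did not answer have the same reasons:

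reported % = r × p, so relative shortfall = 1 − r.

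| r | Source | True 40% reads | Relative shortfall |
|---|---|---|---|
| 0.97 | earlier study | 0.97 × 40% = 38.8% | 3% |
| 0.90 | budget allowance | 0.90 × 40% = 36.0% | 10% |

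These are relative figures; in percentage points they are 1.2 and 4.0. They treat every returned questionnaire as having this item completed. Skipped items would lower r further.

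**4. If non-responders differ.** Take r = 0.90 and a reason held by 40% of responders, so the reported figure is 36%.
- If no non-responder has the reason, the true figure is 0.90 × 40% = 36%, and the shortfall is 0%.
- If all of them have it, the true figure is 36% + 10% = 46%, and the shortfall is 1 − 36/46 = 21.7%.

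So 10% is the value under similarity, not a floor.

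**5. After the correction.** At 90% response the base falls from 6,200 to 5,580, and each percentage rises by the factor 1 / 0.90 = 1.11, so 36% becomes 40%.

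**6. Decline reasons.** About 17,100 − 12,000 = 5,100 decliners are implied. The shortfall equals the share with no reason recorded. The protocol gives no recording rate, so the size cannot be computed; it is zero if every reason is recorded.

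**The case against.** The best defence is that the table's closing phrase serves four items at once and need not mean that non-answers count as not having the reason. A profile of all returners with a not-known row would fit the wording, and missing categories are commonly dealt with in an analysis plan, which is not shown here. This softens the point but does not remove it: the protocol itself fixes the denominator, and on that base each reason's percentage still depends on the response rate.

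It can also be said that the future-preference item is not a perfect model, because its base includes survey returners who sent no swab. That is fair. The matching base here is narrower: swab returners who also answered the item.

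A reader might infer more than the protocol supports:
- **That every reason is understated by at least 10%.** Decline reasons come from GP records, so survey response has no bearing on them. For survey reasons, 10% is not a lower bound: the cited 97% gives 3%, and step 4 shows that a single reason could be affected less.
- **That completer response will be far below 90%.** The sentence expecting fewer returns concerns the sample of completers and non-completers together. Section 9.1.3 cites just under 1% response among non-completers against a 10% allowance, which is enough to explain it. Nothing points to a much lower rate among completers.
- **That groups who answer less will appear to face fewer barriers.** This measure plans no breakdown of reasons by subgroup. The demographic comparisons are in section 9.2.4, among responders, and do not use this denominator.
- **That decline reasons will be patchy.** The logistics condition may refer to whether the field is built at all, and section 14.2 plans drop-down entry linked to the declined code, which favours completeness.

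**Conclusion.** The point holds for the survey-based reasons. Numerator and denominator do not match, and each reason is understated by the share of self-sample returners who did not answer. On the protocol's own response figures that is about 3% (at 97%) to about 10% (at 90%) in relative terms, assuming that women who did not answer resemble those who did.

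For decline reasons the point is conditional: there is an understatement only if some decliners have no reason recorded, and its size is unknown.

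Both measures are exploratory. No primary endpoint or sample-size figure changes. Table 3's implied 6,200 completers are fewer than the roughly 10,000 returns expected elsewhere in the protocol, but that is a separate matter and does not alter the response rates used here.

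**What to change.** In section 3.2, item (iv) of the exploratory row on characteristics and previous barriers, change the denominator to women who returned a self-sample and answered the survey item, and show the number of returners with no answer beside each percentage. Leave the denominators of the NHAIS-based items unchanged.

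In the exploratory row on the opportunistic offer, report each decline reason among decliners with a reason recorded, and show the number unrecorded.

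The cost is two reworded denominators and no new data. The downside is a smaller base, for example 5,580 in place of 6,200 on the Table 3 figures. The percentages then describe women who answered, so the count of non-answers must stay beside them for readers to judge how far they represent all returners.
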